**Methods:**

A single-blind, 18-month, parallel-group cluster randomized controlled trial with 1:1 allocation ratio will be implemented in 2 rural areas of China (Yang County, Shaanxi Province, and Shicheng County, Jiangxi Province). In total, at least 3508 rural caregivers of preschoolers aged 3–6 years old who own a smartphone will be recruited from 24 preschools. Clusters will be randomized at the preschool level and allocated to the control group (receiving routine school-based education plus app-based parenting education excluding unintentional injury prevention) or the intervention group (receiving routine school-based education plus app-based parenting education including unintentional injury prevention). External support strategies will be adopted by local partners to minimize user fatigue, non-compliance, and attrition. Data collection will be conducted at baseline and then every 3 months during the 18-month follow-up time period. Intention-to-treat data analysis will be implemented. Missing values will be imputed by using the Expectation Maximization algorithm. Generalized estimating equation will test the overall effectiveness of the app-based intervention. A per-protocol sensitivity analysis will be conducted to test the robustness of results. Subgroup analyses will follow the strategies for primary analyses. The primary outcome measure is the incidence rate of unintentional injury among preschoolers during the study period. Secondary outcome measures comprise longitudinal changes in caregiver’s attitudes, caregiver-reported supervision behaviors, and caregiver-assessed home environment safety surrounding child unintentional injury prevention in the last week using a standardized audit instrument.

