### Participant recruitment

Eligible participants meet the criteria: being the primary caregiver of a preschooler attending the included schools.

Potential participants will be excluded from this study if they meet any of the following criteria: (1) unwilling to participate in this study; (2) do not own a smartphone or cannot operate the app independently; (3) cannot read text messages; or (4) expect to move to another city with their children during the study time period. If an eligible caregiver care for more than one eligible preschooler, we will enroll only the youngest child.

In coordination with local cooperative partners (governmental departments and agencies), we will recruit class teachers and school staffs to help coordinate recruitment of study participants in each selected preschool. Those individuals will inform eligible caregivers about the study via multiple existing preschool-family communication channels, such as social media platforms (WeChat or QQ), school apps, printed briefing materials and oral notification. Caregivers who agree to participate will be provided an invitation letter that includes the benefits and responsibilities of participating in this study and instructions to download, install, sign up, log in and use the randomly-assigned app. Moreover, all caregivers who agree to participate will receive a short online guidance video that detailedly introduces basic information about the study and educates the participants on how to utilize the app.

When participants log into the app for the first time, they will be invited to complete and submit the informed consent documentation online. All consenting participants will then complete the baseline survey, which collects information about unintentional injuries the child experienced in the past 3 months as well as information on socio-demographic characteristics, caregiver’s attitudes, caregiver-reported behaviors surrounding child unintentional injury prevention, and caregiver-reported home environment safety based on the standardized safety checklist over the prior week.

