### Outcome measure

The primary outcome measure will be the incidence rate of unintentional injury among preschoolers in the past 18 months, which will be calculated by combining data from the six follow-up evaluations accumulatively. We will conduct follow-up evaluations on a quarterly basis (every 3 months) to reduce recall bias in participants remembering children’s minor or moderate injuries [24].

An injury event will be included if it meets any of three criteria [24]: (1) child receives a medical diagnosis or treatment by a doctor or other medical professional following an injury; (2) child receives first aid, takes any injury-related medication, or receives massage or cold/hot compress by a family member, teacher or other non-medical staff following an injury; or (3) child is restricted from school or other activities, or is kept in bed or rest for more than a half-day following an injury. If a caregiver reports that a child experienced more than one unintentional injury event in the past 3 months, we will record the number of injury events but collect specific information only about the most serious one.

Unintentional injury incidence rate will be calculated as “number of preschoolers newly experiencing unintentional injury events divided by total number of preschoolers×100%”.

We also will consider several secondary outcome measures, including: (1) the caregiver’s attitudes toward child unintentional injury prevention, (2) caregiver-reported supervision behaviors related to child unintentional injury prevention in the last week, and (3) the caregiver-reported home environment safety based on a standardized audit checklist over the last week. All secondary outcome measures are based on previously-published and validated items [24, 33–36]. Table 1 lists all planned survey items, with the final survey questionnaire to be refined through a pilot survey, as detailed below.

**Table 1 Tab1:** Survey items assessing child caregiver’s attitudes, supervising behaviors, and child home environment safety

**1. Caregiver’s attitudes** (with four response options: completely agree, partly agree, not sure, and completely disagree)	
a. Preventability of preschooler unintentional injury	
b. Self-efficacy to keep child safe from unintentional injury	
c. Necessity of preventing unintentional injury	
**2. Caregiver’s supervising behavior** (with five response options: always, often, seldom, never, and not applicable)	

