### Collection of formal data

Survey data will be collected at baseline and every 3 months during the entire 18-month follow-up period. All data will be collected online through the app and stored in a password-protected backend database. If caregivers fail to complete an app-based online survey, designated members of the coordinating group will remind or guide them. When needed, a phone-based survey interview will be employed.

Participant engagement data will be gathered and stored in the backend database automatically through embedded tracking of app usage. Data to be collected include: (1) the frequency of logins, (2) time span from login to logout each time, (3) frequency of reading instructional materials, (4) time spent on learning instructional materials, (5) number of reading or bookmarking knowledge disseminations, (6) number of posting comments on knowledge disseminations, (7) number of likes clicked on knowledge disseminations, (8) frequency of joining a discussion in the online forum, (9) number of bookmarked online forum themes, (10) number of comments posted in the online forum, and (11) number of likes clicked in the online forum.

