### Data analysis plan

Primary data analysis will follow an intention-to-treat (ITT) approach. Descriptive statistics will be calculated for socio-demographic variables and primary and secondary outcomes, including mean (or median) and standard deviation (or range and interquartile range) for continuous variables, and frequency and proportion for categorical variables. For each time point, Chi-square and two-sample *t*-tests (or Wilcoxon rank sum test if data are skewed) will be used to examine the differences in outcome measures between intervention and control groups for categorical and continuous variables, respectively. Trend tests or analysis of variance (ANOVA) will used to detect within-group differences across the six follow-up visits.

Generalized Estimating Equation (GEE) will be used to assess the overall effectiveness of the app-based intervention, while adjusting for socio-demographic variables, engagement, and baseline injury events.

A Generalized Linear Mixed Model (GLMM) will be used to verify the GEE results. With GLMM, missing values can be imputed using the Expectation Maximization (EM) algorithm. A per-protocol (PP) sensitivity analysis will be conducted to validate ITT results. All statistical analyses will be performed using R version 4.0.4. All statistical tests will be two-sided at the significance level of 0.05.

Subgroup analyses will be conducted to assess the impact of socio-demographic factors on the intervention effect, including gender and age of children and their caregivers, type of children’s caregivers (e.g., parents, grandparents, or others), education level of caregivers, and household income per capita per month. Subgroup analyses will employ the same statistical methods used for the primary analyses.

This study will strictly adhere to the Consolidated Standards of Reporting Trials (CONSORT) 2010 statement [37] and the Standard Protocol Items: Recommendations for Interventional Trials (SPIRIT) 2013 statement [38] to analyze the data and report the results.

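### No stated analysis adjusts the secondary scores for their own baseline or compares change between arms, although the abstract calls these outcomes longitudinal changes

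*Protocol article*

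**What the plan says.** **Outcome definition.** The abstract (Methods) states: "Secondary outcome measures comprise longitudinal changes in caregiver’s attitudes", and goes on to supervision behaviours and home environment safety. The Outcome measure section introduces the same three with "We also will consider several secondary outcome measures, including" and lists them as measures, without the word change.

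**Data collected.** Under Participant recruitment, "All consenting participants will then complete the baseline survey", which covers attitudes, behaviours and "caregiver-reported home environment safety based on the standardized safety checklist over the prior week". Under Collection of formal data, "Survey data will be collected at baseline and every 3 months during the entire 18-month follow-up period". Each secondary score is therefore due at baseline and at six follow-up visits.

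**Analysis.** The Data analysis plan names three inferential steps:
- tests between arms at each time point (chi-square, t or Wilcoxon);
- trend tests or ANOVA for "within-group differences across the six follow-up visits";
- a GEE for overall effectiveness, "while adjusting for socio-demographic variables, engagement, and baseline injury events", with a GLMM to verify it.

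**The concern.** An outcome described as a change needs either an arm comparison of change or, better, an arm comparison at follow-up adjusted for the baseline value. The plan collects what this requires but states no step that does it. Baseline injury events suit the injury outcome; they are no substitute for a caregiver's own baseline attitude or home-safety score.

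Two things are at stake for the secondary results. The first is precision, because the baseline score usually explains part of the follow-up variance. The second is imbalance. With 12 preschools per arm some chance imbalance is to be expected, and the order of events allows a systematic component. Preschools are allocated once recruited; caregivers are then told how to install the app assigned to them, and they consent and answer the baseline survey at first login. Who enrols could therefore differ by arm.

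The within-arm tests do not fill the gap. They look at one arm at a time and begin at the first follow-up visit, so they miss any shift in the first three months.

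**Working it through.** **1. What each stated analysis does with a secondary score's baseline**

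| Stated analysis | Compares arms? | Adjusts for the score's own baseline? | Estimates change from baseline? |
|---|---|---|---|
| Tests at each time point | Yes, one visit at a time | No | No |
| Trend tests or ANOVA | No, within arm | No | No, six follow-up visits only |
| GEE, verified by GLMM | Yes | Not stated; injury is the only baseline outcome listed | Not stated |

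**2. The plan's own figure.** The Sample size section gives 30% incidence, ratio 0.80 (so 24%), ICC 0.005, cluster size 150, attrition 15% and power 80%; the Data analysis plan adds two-sided 0.05. Design effect = 1 + 149 × 0.005 = 1.745. The pooled two-proportion formula gives 859 per arm: 1718 × 1.745 = 2998, and 2998 / 0.85 = 3527. The unpooled form gives about 3513. The stated 3508 is reproduced closely. It concerns injury only, and this point leaves it unchanged.

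**3. Precision at one visit.** The documents give no baseline-to-follow-up correlation r for these scores; 0.4 to 0.7 is an assumption. The only ICC and cluster size given (0.005 and 150) are for the injury calculation; applying them to the scores is also an assumption.

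With total variance set to 1, the variance of a preschool mean is 0.995/150 + 0.005 = 0.00663 + 0.005 = 0.01163.

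- (a) Only the individual part falls, by the factor 1 − r². SE factor = √[(0.00663 × (1 − r²) + 0.005) / 0.01163].
- (b) The between-preschool part falls in the same proportion. SE factor = √(1 − r²).

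| r | 1 − r² | SE cut, (a) | SE cut, (b) |
|---|---|---|---|
| 0.4 | 0.84 | 5% | 8% |
| 0.5 | 0.75 | 7% | 13% |
| 0.6 | 0.64 | 11% | 20% |
| 0.7 | 0.51 | 15% | 29% |

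Example for (a), r = 0.7: 0.00663 × 0.51 + 0.005 = 0.00838; 0.00838 / 0.01163 = 0.72; √0.72 = 0.85, a cut of 15%. Under (a), a larger ICC would make the saving smaller.

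**4. Size of chance imbalance.** The baseline difference between two arms of 12 preschools has standard error √(2 × 0.01163 / 12) = 0.044 SD, so a 95% range of ±1.96 × 0.044 = ±0.09 SD. At an assumed ICC of 0.05, the preschool-mean variance is 0.95/150 + 0.05 = 0.0563 and the range is ±0.19 SD. An unadjusted follow-up comparison carries roughly r times the imbalance. At the edge of the range that is 0.4 × 0.09 = 0.04 to 0.7 × 0.09 = 0.06 SD for ICC 0.005, and 0.4 × 0.19 = 0.08 to 0.7 × 0.19 = 0.13 SD for ICC 0.05.

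**The case against.** The strongest reply is that the GEE sentence names no outcome. Its covariates fit the injury outcome, and the article may simply not spell out the secondary models, a detail a condensed article can leave to the analysis plan. This stands in part: the text does not prove that baseline scores will be left out. But the article does not merely stay silent. It gives one covariate list for overall effectiveness and one set of visits for the within-arm tests, and neither includes the baseline scores of outcomes that the abstract calls changes.

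A reader might infer more than the documents support:

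- *That baseline scores are used nowhere.* Descriptive statistics and the tests at each time point may include baseline, and a GEE or GLMM could carry baseline as a repeated response. The supportable statement is that no adjustment or between-arm contrast of change is stated.
- *That the arms are never compared on these outcomes.* The visit-wise tests do compare them, and the GEE may.
- *That repeated answers will be treated as independent in the ANOVA.* The plan does not say which form of ANOVA; a repeated-measures form is not excluded.
- *That the methods text contradicts the abstract outright.* The word changes appears only in the abstract, without saying from when. This is a mismatch to reconcile.
- *That the saving in standard error is 8% to 29% without qualification.* That needs the between-preschool variance to fall in proportion; otherwise it is nearer 5% to 15%.

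It is also fair that, under randomisation, a comparison without the baseline score remains valid as far as chance imbalance goes; the cost is a larger standard error. That defence does not cover imbalance from enrolment after allocation, which would be bias. Adjustment removes only the part of that bias that shows in the baseline score.

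**Conclusion.** The point holds for the secondary outcomes only. As stated, the plan neither adjusts the attitude, behaviour and home-safety scores for their own baseline values nor estimates a between-arm difference in change, although it collects what is needed and the abstract describes these outcomes as changes. The likely cost is a standard error reducible by about 5% to 15%, or by 8% to 29% on the more favourable assumption, plus uncorrected baseline imbalance. These figures rest on an assumed correlation of 0.4 to 0.7 and on borrowing the injury ICC and cluster size; some of the gain may already come from the planned socio-demographic adjustment. This is a worthwhile improvement at no design cost, not an error that undermines the trial.

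**What to change.** In the Data analysis plan, for each secondary score:

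1. Fit the GEE or GLMM with preschool clustering and repeated measures accounted for, with arm, visit and arm-by-visit terms and the score's own baseline value as covariate. Alternatively, include baseline as a response with arm-by-visit terms.
2. Report the between-arm difference at each visit and overall.
3. Show within-arm trends from baseline onward as descriptive only, without tests.
4. Align the abstract and the Outcome measure section on whether the outcome is the score or its change.

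Keep baseline injury events as the baseline covariate for the primary outcome. This point takes no position on the engagement covariate.

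The cost is analysis-plan wording. The baseline scores are already in the survey schedule, and the sample size does not change.

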### Sample size

Based on previous literature [29], we conservatively hypothesize that the unintentional injury incidence of rural preschoolers aged 3–6 years old in project sites is 30% in the past 18 months. On the basis of a previous report [30], we assume the effect size of the app intervention to be 0.80 (incidence rate ratio) compared to traditional unintentional injury prevention intervention. In addition, we assume an intra-class correlation (ICC) of 0.005 with a cluster size of 150 children per preschool [31], and an allocation ratio of 1:1 between intervention and control groups. Considering extensive strategies will be adopted to increase retention in the study, we assume an attrition rate of 15% for the 18-month follow-up. Given these assumptions, a minimum sample size of 3508 caregivers is needed for the study to achieve a statistical power of 80% at the 0.05 significance level. As many rural preschools have more than 150 children in the study sites we select, 24 preschools will be ample to recruit the needed sample size.

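### The subgroup plan asks whether socio-demographic factors change the app's effect, but the only method it gives is the overall-effect analysis, which does not test that

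*Protocol article*

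**What the plan says.** The Data analysis plan gives the aim: "Subgroup analyses will be conducted to assess the impact of socio-demographic factors on the intervention effect". It lists seven factors: the sex and the age of the child, the sex and the age of the caregiver, caregiver type, caregiver education, and household income per head. The method follows: "Subgroup analyses will employ the same statistical methods used for the primary analyses". The Methods part of the abstract repeats it: "Subgroup analyses will follow the strategies for primary analyses".

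The primary method, in the same section, is a GEE for the overall effect of the app. It adjusts for socio-demographic variables, engagement and baseline injury, and a GLMM serves as a check. Socio-demographic variables enter only as adjustments. Every test is two-sided at 0.05. The article mentions no arm-by-factor term and no comparison between subgroups.

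**The concern.** Whether a factor changes the intervention effect is a question about a difference between effects. A model for the overall arm effect, fitted within one subgroup, answers another question: is there an effect here? If the model is fitted in each subgroup in turn, the only evidence about effect modification is that one result is significant and another is not. Two subgroups with the same true effect will often differ in that way, because each has less power than the whole trial.

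The primary conclusion is not at risk. What is at risk is a planned set of results on who benefits, which could report differences that come from chance and reduced sample size.

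**Working it through.** **Inputs (Sample size section).** Control incidence: "in project sites is 30% in the past 18 months". Effect: "we assume the effect size of the app intervention to be 0.80 (incidence rate ratio"), so 30% against 24%. Clustering: "intra-class correlation (ICC) of 0.005 with a cluster size of 150 children per preschool". Attrition: "we assume an attrition rate of 15% for the 18-month follow-up". Total 3508, 24 preschools, 1:1, 80% power, two-sided 0.05.

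**Step 1: the plan's own figure.** With unpooled variance, n per arm = (1.960 + 0.842)² × (0.30×0.70 + 0.24×0.76) / 0.06² = 7.849 × 0.3924 / 0.0036 = 855.5. Design effect = 1 + 149 × 0.005 = 1.745. Total = 2 × 855.5 × 1.745 / 0.85 = 3513. The pooled-variance form gives 859 per arm and 3527. Both are within about 0.5% of 3508, so the inputs are read as the plan used them.

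**Step 2: power in half the sample.** The article gives no subgroup sizes. I assume a two-level factor, split 50:50 within every preschool, with 30% against 24% in both halves.

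- Retained: 3508 × 0.85 = 2982, or 1491 per arm.
- Per arm in one half: 745; per preschool, 745 / 12 = 62.1.
- Design effect in a half: 1 + 61.1 × 0.005 = 1.306.
- Effective number per arm: 745 / 1.306 = 571.
- Standard error: √(0.3924 / 571) = 0.0262.
- Expected z: 0.06 / 0.0262 = 2.29.
- Power: Φ(2.29 − 1.96) = 0.629, about 63%.

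**Step 3: how often the halves disagree.** Both halves come from the same 24 preschools, so their estimates share the preschool component. Their correlation is ICC / (design effect / m) = 0.005 / (1.306 / 62.1) = 0.24. For two normal statistics with mean 2.29 and correlation 0.24, the probability that both exceed 1.96 is 0.430. The probability of exactly one significant result is 2 × (0.629 − 0.430) = 0.398, about 40%.

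| Situation | Exactly one half significant |
|---|---|
| Same effect in both, shared preschools | about 40% |
| Same effect in both, halves independent: 2 × 0.629 × 0.371 | about 47% |
| Same effect in both, no clustering (power 74%): 2 × 0.742 × 0.258 | about 38% |
| No effect in either, halves independent: 2 × 0.05 × 0.95 | about 9% |

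In the last row, allowing for the shared preschools still gives about 9%.

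**Step 4: the alternative.** A two-sided 0.05 interaction test declares a false difference in about 5% of trials, whether or not the app works. Simulation with independent halves gave 4.9% in both cases.

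**Step 5: seven factors.** If the factors were independent, seven unadjusted interaction tests would give at least one false positive with probability 1 − 0.95⁷ = 0.30. The interaction test therefore does not remove the need to call these results exploratory.

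**The case against.** The strongest objection is that the text never says what is being criticised. A GEE or GLMM can carry an arm-by-factor term, and an aim stated as impact on the intervention effect is itself interaction language. A reader might infer that the plan rules out interaction tests, or that p-values will be compared across subgroups. The article says neither. Nor is an unnamed model term in a condensed article a fault in itself, since such detail may sit in a fuller document.

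That limits the point but does not remove it. The article does not leave the subgroup method open. It states one, twice, by reference to an analysis described only in terms of the overall effect. Followed as written, that method does not answer the stated question. A fuller plan with interaction terms would add something these sentences do not contain.

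Three further limits stand:

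- **Size.** It is tempting to treat the halves as independent, which gives 47%. For a factor that varies within preschools this is too high, and 40% is the better figure. Frequent disagreement also depends on the app working; with no effect the figure is about 9%.
- **Multiplicity.** Adding up the chance of any significant subgroup result measures something else. It would also need independent two-level factors. Every child appears under all seven factors, and caregiver type is listed with three example categories.
- **Consequences.** A reader might infer that a false message, such as benefit for parents but not grandparents, is the likely product. The documents do not support this. In the abstract and the Discussion, distribution depends on the app being effective, not on subgroup results.

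**Conclusion.** The point holds in this form: the stated aim is effect modification, the stated method estimates the overall arm effect, and nothing in the article connects the two. On the natural reading, and if the app works equally well in two equal subgroups from the same preschools, their significance results disagree in about 40% of trials, against about 5% for an interaction test.

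The 40% rests on the plan's incidence, effect, ICC and attrition, on an assumed 50:50 split within preschools, and on a normal approximation. It depends little on the ICC, since 38% remains with no clustering at all. This is a correction worth making to a secondary analysis. It is not a flaw in the primary comparison, and it does not show that the investigators intend to compare p-values.

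**What to change.** Replace the sentence on subgroup method with one stating that each subgroup question is answered by an arm-by-factor interaction term in the full-sample primary model, with clustering by preschool, reported as an estimate with its confidence interval. Add that subgroup-specific ratios with confidence intervals are descriptive, and that all subgroup results are exploratory because seven factors are examined. Bring the abstract into line.

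The cost is a few sentences, with no new data or participants. The downside is low power for interactions and fewer nominally significant subgroup results. As a rough guide under the assumptions above, the standard error of the difference between two half-sample effects is 0.0262 × √(2 × (1 − 0.24)) = 0.0323. Even a full 6-point difference (the planned effect in one half, none in the other) gives z = 0.06 / 0.0323 = 1.86 and power of about 46%. A non-significant interaction should therefore not be reported as evidence that effects are equal.
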